### Outcomes

All outcomes of the study will be assessed at the starting point, and after 2 weeks and 3 months. Participant characteristics and demographic variables will be collected at baseline. Participant characteristics include age, gender, and relevant comorbidities, while demographic variables include job category, work experience, academic qualification, job title, and the number of local training courses. The outcomes are based on the recommendations of the NPT and its 4 related constructs [58].

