### Sample Size

The study has been designed as a superiority trial with 2 parallel groups (ELNEC-PPC web-based training plus usual care and usual care only). For calculation of the appropriate sample size, the main researcher uses the assumption that the 5 selected settings have 254 nursing staff members on average eligible for inclusion based on a survey of all included settings before the study to determine the total number of nurses who work in the selected settings and are appropriate for inclusion. Based on this assumption, as well as a 2-sided *P* value <.05, a 0.90 power, a traditional predictable correlation between 2 measurements of 0.5, and an intraclass correlation coefficient with *P*<.05, 86 participants were required in the intervention group and 86 were required in the control group for *t* tests. To support equal sample sizes, including for the units of the selected settings, and to account for intrastratified correlations of units, a multilevel analysis will be used. Nursing staff members who are transferred to a dissimilar organization unit will be exchanged from the sample of nursing staff, and changes will take place in the course of the study. To catch up with nursing staff members who are not changed in time, the researchers will insert an additional organization unit from the critical care units for the intervention and control groups, which will result in a total of 172 nursing staff members. All power analyses will be performed using the G*Power software (version 3.1).

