### Data Collection

#### NoMAD Instrument

Participants will complete 2 data collection forms at the beginning, and forms will also be completed after the ELNEC-PPC training. The main data collection instrument is NoMAD [33]. The original form of this instrument has been translated into Arabic and adapted to Arabic conditions to evaluate the normalization potentiality of PPC training, which will be provided by a web-based training intervention.

The NoMAD instrument has been translated into the Fusha dialect in translation steps outlined previously [60]. The authors translated the NoMAD instrument from English to Arabic, and then, back translated it to English. The content validity and translated NoMAD acceptability have been measured in a reiterative procedure involving several recognized steps, including translation forward and translation backward, tests of the target language instrument content validity, meetings with specialists, and further revision, as well as a final content validity test of the studied tool. The finalized tool has been created as an electronic form. The Arabic NoMAD prime version, following step 2 of the clarification and adaptation process, has been applied in a pilot study. The Arabic NoMAD instrument is split into the following 3 sections: Section A, which includes 12 items on the respondents; Section B, which includes 3 general items on the intervention; and Section C, which includes 20 identifiable items on the intervention. Regarding the 4 NPT concepts, “Coherence” has 4 questions, “Cognitive Participation” has 4 questions, “Collective Action” has 7 questions, and “Reflexive Monitoring” has 5 questions.

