Repeated measures ANOVA will be performed to assess the multivariate main intervention effects (associated with controls) considering pre, post, and follow-up time points, as well as their interface effects. A 2-sided *P* value <.05 will be considered significant. The standardized effect size (Cohen *d*) will also be calculated. Mediator analysis will be controlled to determine which subgroups would benefit further from the intervention, with outcome variables regressing on independent variables, including age group, sex, education, and starting Arabic NoMAD score.

Secondary outcomes will be analyzed using an approach similar to the approach described for the primary outcome with linear mixed models for repeated measures. The data from the 2-week and 3-month follow-ups will also be analyzed using the approach described above for the primary outcome.

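### The analysis of which nurses benefit more enters age as an undefined age group although age itself is listed as collected; if it is held in years, grouping it loses information

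*Protocol article*

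**What the plan says.** The Statistical Analysis section of the protocol article describes one analysis of differential benefit: "Mediator analysis will be controlled to determine which subgroups would benefit further from the intervention". It is to be done "with outcome variables regressing on independent variables", and the regressors are given as "including age group, sex, education, and starting Arabic NoMAD score". No arm-by-covariate term is written. The section states no number of age groups and no boundaries.

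The Outcomes section describes the baseline data differently: "Participant characteristics include age, gender, and relevant comorbidities". It names age, not a grouping of age. The NoMAD Instrument section mentions "Section A, which includes 12 items on the respondents" but does not describe their response format, so the unit in which age is held is unknown.

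The Sample Size section gives "a 0.90 power, a traditional predictable correlation between 2 measurements of 0.5" and concludes that "86 participants were required in the intervention group and 86 were required in the control group" for t tests. That calculation serves the two-arm comparison. No power is given for the analysis of who benefits more.

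**The concern.** Grouping a numeric modifier treats every nurse within a band as the same age and puts a step at each boundary. If the benefit changes smoothly with age, part of the variation that could reveal this is thrown away. The estimate also depends on where the boundaries fall, a choice that need not be made at all if age is kept in years.

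What is at stake is limited. It is the precision and stability of one covariate's result in a secondary analysis, in a trial that was not sized for that analysis.

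**Working it through.** **The plan's own figure.** The only related figure is 86 per arm, and the protocol gives no effect size to reproduce it from. If a standardised difference of 0.5 is assumed, with two-sided 0.05 and power 0.90, the normal approximation gives 2 × (1.960 + 1.282)² / 0.5² = 84.1, so 85 per arm. The exact t calculation gives 86 (power 0.903). The figure is therefore consistent with a main-effect t test, but the 0.5 is an assumption.

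**Information kept by grouping.** Inputs that the protocol does not give, and which are assumed here: a linear age effect, equal-sized groups, and the shape of the age distribution. The share kept is the between-group variance of age divided by its total variance, Σ pₖmₖ² for standardised age, where pₖ is the share of nurses in group k and mₖ the group mean.

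- Two groups, normal age: the group means are ±√(2/π) = ±0.798, so the share kept is 2/π = 0.637.
- Three groups, normal age: the outer means are ±1.091 and the middle mean is 0, so the share kept is (2/3) × 1.091² = 0.793.
- *k* groups, uniform age: the share kept is 1 − 1/k².

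The loss is 1 minus the share kept. The effective number is 172 times the share kept.

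| Equal groups | Loss, normal age | Loss, uniform age | Loss, right-skewed age (gamma, shape 2) | Effective number out of 172 (normal age) |
|---|---|---|---|---|
| 2 | 36% | 25% | 45% | 109 |
| 3 | 21% | 11% | 28% | 136 |
| 4 | 14% | 6% | 21% | 148 |
| 5 | 10% | 4% | 16% | 154 |

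Unequal groups can lose more: with normal age, a single cut at 30/70 loses 42% and one at 20/80 loses 51%.

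**Power of the age-by-arm test.** Let b be the difference between arms in the slope of the outcome, in outcome SDs per SD of age. With 172 nurses allocated 1:1 and no dropout, the noncentrality is 172 × b² × (share kept) / 4. The significance rule is the plan's: "A 2-sided *P* value <.05 will be considered significant".

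For b = 0.3 (assumed) and normal age:

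- Continuous age: noncentrality 172 × 0.09 / 4 = 3.87, power 0.50.
- Two groups: 3.87 × 0.637 = 2.46, power 0.35.
- Three groups: 3.87 × 0.793 = 3.07, power 0.41 as a linear score or 0.32 as a 2-df factor.
- Four groups as a 3-df factor: 3.87 × 0.861 = 3.33, power 0.30.

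Over other assumed slopes, continuous age against two groups gives 0.26 against 0.18 at b = 0.2, 0.74 against 0.55 at b = 0.4, and 0.90 against 0.74 at b = 0.5. The last value means that the training effect differs by 2 × 0.5 = 1.0 SD between nurses one SD above and one SD below the mean age. That is twice the main effect of 0.5 assumed above.

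A cruder check agrees. For a 0.5 SD difference in effect between two equal halves of the sample, with 43 nurses per cell, the standard error is √(4/43) = 0.305. Then 0.5/0.305 − 1.96 = −0.32, a power of about 0.37.

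**The case against.** The strongest reply is that the protocol never says age is recorded in years. If the questionnaire collects it in bands, age group is simply the variable as collected: nothing is discarded at analysis and no boundary is chosen afterwards. This stands, and it is why the point is conditional.

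A second reply is that covariate coding and cut points belong in an analysis plan that is not shown, and that this is a condensed article. That disposes of any complaint about missing boundaries. It does not dispose of the stated choice to enter age as a group. The wording around it is loose, and a sentence about subgroups naturally mentions groups, so the choice may not have been deliberate. That is a reason to settle it, not to keep it.

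A third reply is that the plan writes no age-by-arm term, so recoding age alone would not show who benefits more. This is correct, and the fix has to include that term.

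Two stronger readings are tempting. A reader might infer that a fixed share, say a fifth to a third, of the information is being lost. That needs two or three equal groups and near-normal age, and the protocol gives neither. A reader might also infer that the starting NoMAD score is kept continuous while age is not. The text does not say it is grouped, but neither does it say how it enters.

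**Conclusion.** The point holds as a conditional and minor one. The protocol lists age as collected and enters an undefined age group. If age is available in years, that coding is less efficient than it need be and leaves the result open to the choice of bands.

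The size is not known from the document. It is about 10% to 36% for 5 down to 2 equal groups with near-normal age, and about 4% to 45% once uniform and moderately right-skewed shapes are allowed, all under a linear age effect. Low power under either coding also rests on an assumption, a slope difference of about 0.3 SD per SD of age. The dropout that the Discussion expects to be high would lower these powers further.

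A reader might take this as a threat to the trial's main result. It is not: the NoMAD comparison at 3 months does not involve this coding.

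**What to change.** In the Statistical Analysis section, replace *age group* with *age in years (continuous)*, entered with its interaction with trial arm. Use a linear term, or a 3-knot spline if linearity is doubted. Present the estimated arm difference with its 95% CI at two or three ages chosen in advance, which serves a reader who wants groups.

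If age was recorded only in bands, say so and use those recorded bands, fixed before the analysis.

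If years are on file, the cost is a change of wording and one model term, with no new data. The downside is an assumed functional form for age; the spline relaxes it at the price of an extra interaction parameter. The change does not make this analysis well powered, so its result should still be read as exploratory.

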### Pilot Testing

A pilot study was conducted between March 2020 and July 2020, by using the initial Arabic NoMAD version, following clarification and adaptation. This pilot study was the initial implementation of the PPC web-based training intervention.

The web-based training intervention was used for the provision of PPC in hospitals by staff nurses, and for the application and development of further adaptable and improved operating approaches in health care facilities.

The pilot study was performed to test the instruments, make revisions where necessary, and again test the instruments. Other aspects of the research, such as how to gain access to respondents, were also piloted. Moreover, we tested a process to implement the ELNEC-PPC web-based training intervention, and to gain information about practical procedures regarding recruitment and screening as described in this protocol. Accordingly, the pilot study identified challenges in the recruitment process that could be addressed before the RCT.

The pilot study was conducted with the methods described for the RCT in this protocol. Recruitment ran until testing from all described channels. All participants in the pilot study contributed to the ELNEC-PPC web-based training and usual care (intervention). Outcome data were collected at baseline and after 2 weeks. The outcome data collected will not be included in the RCT analysis.

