### Study Setting

The trial will take place in selected Hillah city hospitals, which are local government organizations that have various pediatric and adult sections. In Iraq, there are 273 public hospitals spread all over the country [51]. Hillah city in Babylon province has 4 hospitals and 1 Babylon Oncology Center. The recruitment of participants will be conducted at the following 5 locations: Imam Sadiq Teaching Hospital (general hospital) with 492 beds, Babylon Maternity and Children Teaching Hospital (obstetric and pediatrics hospital) with 323 beds, Morgan Teaching Hospital (specialized center for tertiary health care), Al-Noor Hospital for Children (pediatrics hospital), and Babylon Oncology Center [52].

Participants will be recruited and stratified into the following groups: (1) critical care units (1 artificial kidney unit, 1 resuscitation emergency unit, 1 catheterization unit, 2 children’s emergency units, 1 emergency department, 1 maternity emergency unit, 1 morning resuscitation unit, 1 operation room, and 1 pediatric surgery unit); and (2) noncritical care units (1 blood disease unit, 1 chemo injection unit, 1 health insulation unit, 1 private suite, and 5 pediatric lobby units). Staff in the selected hospitals are not employed in 2 areas at the same time, and pediatric patients with several diagnostic classifications are managed and provided usual care. Recruitment for this study started in July 2020. There is a 2-year outline plan for the research, with likely changes along with primary analysis outcomes.

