### Inclusion and Exclusion Criteria

The study will include nurses who (1) have been employed by Imam Sadiq Teaching Hospital, Babylon Maternity and Children Teaching Hospital, Al-Noor Hospital for Children, Morgan Teaching Hospital, and Babylon Oncology Center; (2) have completed their bachelor’s degree and have a master’s or doctorate degree in nursing sciences; (3) have been working for at least 3 months and are not expected to be moved to another internal unit during the research period (including morning and evening shifts); (4) provide nursing care for both male and female hospitalized patients aged ≤18 years; (5) use a computer (desktop or laptop) with access to the internet at home or work (phone line or internet access), or use a smartphone (Android 6.0+ or iOS 11.0+) with internet access (Wi-Fi or mobile data) to join the online training course; and (6) have a working email address or a working mobile number, and have access to a computer or smartphone with internet access to complete questionnaires in a web browser.

The study will exclude nurses who (1) are not interested; (2) are not employed for at least 3 months; (3) work in units other than the selected units; and (4) are enrolled in another experimental trial.

The evaluation of whether the exclusion criteria are met is performed by the investigator during the recruitment phase or according to the participant’s responses during the interview.

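### The eligibility criteria do not keep pilot nurses, all of whom took the ELNEC-PPC course, out of the RCT; any allocated to usual care would dilute the 3-month contrast

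*Protocol article*

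**What the plan says.** Pilot Testing describes a single-arm run of the trial intervention: "All participants in the pilot study contributed to the ELNEC-PPC web-based training and usual care (intervention"). On timing, "A pilot study was conducted between March 2020 and July 2020", while Study Setting states "Recruitment for this study started in July 2020". On the source of the pilot nurses, the section says "The pilot study was conducted with the methods described for the RCT in this protocol" and "Recruitment ran until testing from all described channels". It gives neither the pilot hospitals nor the pilot size.

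The only separation between pilot and trial is at the level of data: "The outcome data collected will not be included in the RCT analysis".

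Inclusion and Exclusion Criteria gives six inclusion and four exclusion criteria. The exclusions begin "The study will exclude nurses who (1) are not interested; (2) are not employed for at least 3 months" and end "3) work in units other than the selected units; and (4) are enrolled in another experimental trial". None of the ten criteria refers to the pilot or to earlier ELNEC training. Randomization is stratified by unit type only. Under Usual Care, controls are to get access to the course only after the trial is complete.

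**The concern.** The comparison is between nurses who have had the course and nurses who have not. The plan protects this by withholding the course from controls until the end, but it sets no matching condition at entry. A nurse trained in the pilot weeks or months earlier meets the criteria as written and can be allocated to usual care. Under the intention-to-treat analysis she counts as an untrained control at 3 months although she has been trained. The usual-care mean then shifts toward the intervention mean, and the estimated effect is too small.

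Earlier training is not a stratification factor, so the design would not balance it either. The number of local training courses is collected at baseline (Outcomes), but the article attaches no rule to it.

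**Working it through.** **Inputs from the protocol article**
- Eligible nurses: 254 (Sample Size).
- Planned size: 86 per arm, 172 in total, for t tests, two-sided 0.05, power 0.90, correlation between two measurements 0.5 (Sample Size).
- Primary estimate: between-group mean difference in NoMAD score at 3 months (Statistical Analysis).
- 30 people have completed the Arabic NoMAD survey (NoMAD Instrument).

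**Assumptions, none stated in the article**
- Standardized effect d = 0.50. The article gives no effect size.
- k pilot nurses are among the 254, with k from 10 to 30. The upper value treats the 30 survey completers as the pilot nurses.
- Pilot nurses enrol at the same rate as the others and are split evenly by randomization.
- The effect of the pilot course persists in full, and taking the course again adds nothing.
- Clustering and dropout are ignored.

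**Step 1. The planned size.** Without a stated effect size, 86 cannot be reproduced from the article's inputs alone. With d = 0.50, the exact two-sample t test has power 0.8999 at 85 per arm and 0.9032 at 86. So 86 is the smallest size reaching 0.90, and d = 0.50 is a reasonable working value.

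**Step 2. Which arm causes the dilution.** Let a fraction f of each arm be trained in the pilot.
- A pre-trained control ends at the trained level, so the control mean rises by f × d.
- If retraining adds nothing, a pre-trained intervention nurse also ends at the trained level, where the course puts every other intervention nurse. The intervention mean does not change.
- The expected contrast is therefore d × (1 − f), with f = k/254. The loss comes from the control arm alone.

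**Step 3. Power at 86 per arm.** The unadjusted column uses the noncentral t with the diluted d. The adjusted column divides d by √(1 − 0.5²) = √0.75, an approximation to baseline adjustment at correlation 0.5.

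| Pilot nurses among 254 | Loss of contrast | Expected pre-trained controls (86 × k/254) | Diluted d | Power, unadjusted | Power, adjusted |
|---|---|---|---|---|---|
| 0 | 0% | 0 | 0.50 | 0.903 | 0.964 |
| 10 | 3.9% | 3.4 | 0.480 | 0.879 | 0.951 |
| 20 | 7.9% | 6.8 | 0.461 | 0.852 | 0.934 |
| 30 | 11.8% | 10.2 | 0.441 | 0.820 | 0.913 |

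A less favourable case has all 30 enrolled, 15 per arm. Then f = 15/86 = 17.4%, d = 0.413, and unadjusted power is 0.77. If no pilot nurse is in the pool, there is no loss.

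**Step 4. Room to exclude.** Removing 30 leaves 254 − 30 = 224, still above 172. Required uptake rises from 172/254 = 68% to 172/224 = 77%.

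**The case against.** **The article does not show that any pilot nurse entered the RCT.** This is correct. It names no pilot site and gives no pilot size, and it does not say whether pilot nurses are counted in the 254. The reference to the RCT's methods cannot be fully literal, since the pilot had one arm and no 3-month outcome. Overlap of the two pools is an inference from the shared methods and channels, and from pilot and trial training being described as one sequence in the Discussion.

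**The eligibility explanation sent to the hospital education units, or the full protocol, may deal with this.** That is possible. But the article sets out the criteria as numbered lists, and it addresses the pilot only by excluding its data.

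**The fourth exclusion may cover the pilot.** Someone screening in July 2020 might apply it that way. It is worded for current enrolment in another experimental trial, though, and does not clearly reach a nurse who has finished an uncontrolled pilot of the same project.

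**A reader might infer that pre-trained nurses in both arms pull the difference toward zero.** The planned 3-month contrast does not support this. If retraining adds nothing, pre-trained intervention nurses still end at the trained level, and counting them would count the same loss twice.

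**The unadjusted t test understates the planned analysis.** This stands. Statistical Analysis describes a repeated-measures mixed model that uses the baseline score, and with baseline adjustment at r = 0.5 power stays at about 0.91 in the 30-nurse case.

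**Conclusion.** The point holds as a gap in the eligibility criteria: as written, they admit a nurse already trained in the pilot and allow her to be allocated to usual care. If that happens, the 3-month effect is biased toward zero.

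The size is conditional and moderate. With d = 0.50 and 10 to 30 pilot nurses among the 254, the contrast falls by 4% to 12%. The corresponding power is 0.88 to 0.82 (from 0.90) unadjusted, or 0.95 to 0.91 (from 0.96) adjusted. These figures rest on the assumed effect size, the assumed number and source of pilot nurses, and full persistence of the pilot training.

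A reader might go further and infer that the trial was in fact contaminated, or that it is likely to miss a real effect for this reason. The article supports neither: it reports no such enrolment, and most of the planned power survives in the cases tabulated.

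**What to change.** **Before randomization.** Add an exclusion criterion for nurses who took part in the pilot or have already completed an ELNEC course, and check the nomination list against the pilot list. This costs one line and one list comparison. The downside is the smaller pool: with 30 removed, uptake has to be 77% instead of 68% to reach 172. If the pilot nurses came from outside the five settings, one sentence saying so settles the matter.

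**For nurses already randomized.** The Discussion gives August 2020 for the last training, so a check at entry may come too late for some or all. In that case, identify pilot participants by arm, report the counts, keep the intention-to-treat analysis as primary, and add a sensitivity analysis that removes them from both arms. Pilot participation is fixed before randomization, so removing it symmetrically keeps the comparison randomized. The cost is a somewhat smaller sample in that analysis.
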